**Figure 4 figure4:**
[figure not shown]
An overview of the structure of the data-collection system. The system consists of three independent systems: (1) a Linux system, (2) an android system acting as a temporary server, and (3) a Bluetooth low-energy system consisting of independent wearable devices.

This database will be granulized and compressed into a format that can be used in further analyses, including structuring the information, developing the metadata, and ensuring anonymity of the data. For example, rather than knowing the exact date of the measurement, only the time of the day and season will be recorded when analyzing walking habits.

### Data Verification

Data verification requires confirming that the measured signals have the appropriate quality to accurately distinguish walking segments from other movements and to use the signals for further analysis. The possible issues faced during home or clinic measurements are also recorded and analyzed, including, for example, usability issues with the technology as reported by the participants or network issues leading to the loss of data. These analyses would confirm that there is an appropriate amount of high-quality data that is usable in machine learning applications. If any such problems are identified in the measurement setup, they will be fixed to ensure the quality of the data.

The collected signals are checked both visually and statistically to assess whether they contain the necessary information for the classification of different types of movements. A minimum sampling frequency of 50 Hz was required for the measurements conducted with the smartphone based on the previous studies presenting human walking under 10 Hz [29] and hand tremors in PD under 20 Hz [30]. The measurements will be discarded if they are below a 50-Hz sampling frequency. Suunto Movesense and Forciot use their own sampling frequencies of 52 Hz and 50 Hz, respectively.

Information is collected on how many files were successfully recorded during a 3-day measurement. Successful measurements are defined as those that are recorded and transferred correctly and have the appropriate sampling frequency. This information is used to monitor how well the measurement system functions when the subject is responsible for merely charging the smartphone and restarting it if the power runs out. The performance analysis includes battery life, possible network issues, and usability issues. These properties are studied and used in further development of the measurement system.

### Data Analysis

Methods for data analysis are developed and structured based on a data-analysis pipeline. This pipeline includes data preprocessing, walking detection, calculation of features related to changes in walking, and feeding the features into a machine-learning system to classify the symptoms and subjects. The classification results and the performance of the classifier are then analyzed. The main features of data analysis include the identification of patients with PD from healthy subjects based on sensor data and prediction of UPDRS scores from the sensor data. The long-term target is to build an automated classification system that could support home monitoring by using machine learning methods. All the data analysis will be done in Python 3 (Python Software Foundation, Wilmington, DE) and MATLAB (The MathWorks, Inc, Natick, MA).

We will be using a data-driven approach to analyze and compare a large number of features calculated from the signals of the different sensors. However, we will consider possibilities to combine the information of different sensors to define such features or parameters that are likely relevant to PD, for example, the amount of arm swing during walking. The incompleteness of the data set (wrist and insole sensors not included in all the recordings), however, limits the use of parameters requiring combining sensor information. This will be discussed in future publications on the data analysis.

The preprocessing phase includes the signal-processing steps that are required before the signals can be used in further data analysis. The signals are resampled to obtain a constant sampling frequency; simultaneously measured signals are aligned to have the same starting and ending time; and, if necessary, the signals can be filtered with a basic low- or high-pass filters.

An accurate walking-detection algorithm and careful selection of machine-learning features are important when developing the data-analysis pipeline. Activity-detection algorithms have already been developed by other research groups, for example, based on the mean amplitude deviation [31-32], which is more thoroughly defined in another previous study [33]. An algorithm based on the existing literature will be developed and implemented during this study. The walking-detection algorithm may extract either walking segments or individual steps. When recognizing the walking patterns from home data, we may use the 20-step walking tests as a personal reference of the subject’s walking style. Walking detection from the 20-step tests is rather easy, since the signals only contain walking or standing. Walking detection will be thoroughly analyzed and discussed in future publications considering the analysis of data from home measurements.

The selection of features is also important when building a machine-learning system for health care use. The features should describe real physiological changes in the walking patterns; for example, if the patient is in the On state with good balance in the medication, his/her walking is classified as better than the same patient without the medication (Off state). Although On and Off states are not specifically defined in this study, we aim to recognize the differences before and after taking the medication. Features can be selected with a statistical approach, for example, by applying the minimum Redundancy Maximum Relevance algorithm [34] or the theoretical understanding of PD to choose features related to the physiological changes in the patients. Features may include both statistical features of the signals such as mean, median, or SD, or they can be defined from the physiology and be based on traditional features used in gait analysis, such as step length or speed.

The subjective UPDRS classification performed by the physiotherapist is used to test the classification of the subjects from the 20-step walking tests. The UPDRS score can be used as the true label of the subject’s current state, and the walking tests are classified into several groups identifying the severity of motor symptoms in walking. In home measurements, the UPDRS score defined at the clinic may be used to test whether the classification result before taking the PD medication differs from that soon after taking the medication. Alternatively, unsupervised learning methods such as clustering approaches may be used to study whether there are differences in the feature values before and after taking the medication.

The classification phase includes applying different machine learning classifiers to study the most feasible method for classifying the symptoms and changes in symptoms related to medication intakes. For example, a support vector machine [35] and random forest [36] will be used to classify walking patterns. Classification performance is evaluated by a confusion matrix and the metrics related to it including accuracy, sensitivity, specificity, and the receiver operating characteristic curve. Other measures may be added to evaluate the performance more thoroughly.

The data analysis aims to develop methods to answer the following hypotheses: (1) Can we distinguish patients with PD from healthy controls by using wearable sensors and machine learning classifiers? (2) Can we assess the severity of symptoms before and after medication intake? These key hypotheses may be further specified or expanded in further analyses. These methods, combined with the novel data-collection method, can be further developed into a home-monitoring system for health care professionals and neurological patients.

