**Objective:**

The primary objective of this study is to collect a dataset for developing methods to detect PD-related symptoms that are visible in walking patterns at home. The movement data are collected continuously and remotely at home during the normal lives of patients with PD as well as controls. The secondary objective is to use the dataset to study whether the registered medication intakes can be identified from the collected movement data by looking for and analyzing short-term changes in walking patterns.

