### Study Design

A study sample of 150 subjects will be recruited, of which 100 will be patients with PD and 50 will be healthy controls. Approximately 50 of the patients with PD will be in an early stage of the disease and the other 50 will be in a progressed stage of the disease. This classification is based on the modified Hoehn and Yahr Staging of PD [18], where patients with a score of 0-2 are considered to be in the early or mild stage of the disease, and patients with scores of 2.5-5 are considered to be in the progressed or more severe stage of the disease. Both the study and control groups go through the same measurement protocol, including a clinic visit with questionnaires and tests and a home measurement for 3 consecutive days. The home measurement period aims to record data showing short-term changes in walking patterns related to the On/Off state changes or wearing-off effect of medication. In addition, the period can be used to evaluate the subjects’ physical activity at home. Figure 1 presents the study protocol.

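### The before/after-intake comparison has no time-matched reference, so a difference could reflect time of day rather than medication

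*Protocol article*

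**What the plan says.** The abstract's Objective sets the secondary aim: to "study whether the registered medication intakes can be identified from the collected movement data by looking for and analyzing short-term changes in walking patterns". In the Data Analysis section the second hypothesis reads "Can we assess the severity of symptoms before and after medication intake". Two optional routes follow. In the first, the clinic UPDRS score "may be used to test whether the classification result before taking the PD medication differs from that soon after taking the medication". In the second, "clustering approaches may be used to study whether there are differences in the feature values before and after taking the medication".

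The same section says: "Although On and Off states are not specifically defined in this study, we aim to recognize the differences before and after taking the medication". Intake time is therefore the only label for drug state in the home data. The UPDRS is scored once, at the clinic.

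Neither route names a reference without intake, control windows at the same clock time, or an adjustment for time of day. The material for such a reference exists:
- Study Design says "Both the study and control groups go through the same measurement protocol", and this includes the 3 home days.
- Data Collection and Management keeps clock time in the de-identified data: "only the time of the day and season will be recorded when analyzing walking habits".
- Intake is registered both in the app and in a paper diary (Study Design).

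**The concern.** Intakes are self-timed in daily life and not randomised, so they may follow waking, meals and rest. Walking may change across those times with no drug effect. Study Design also says the sensors are not worn during sleep. For any dose taken soon after waking, the before period would then hold little recorded walking, or only walking just after getting up.

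With no independent On/Off label and no reference at the same clock time, the stated contrast cannot separate a response to medication from the time of day. This matters because the Discussion expects the dataset to lead to tools that help adjust medication. A detector that had partly learned the clock would serve that purpose poorly.

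**Working it through.** **Figures in the plan.** No significance level, power, effect size or SD is given, so there is no plan figure to reproduce. The only stated inputs are the sample ("A study sample of 150 subjects will be recruited, of which 100 will be patients with PD and 50 will be healthy controls"; 100 + 50 = 150) and the 3 home days. Everything else below is assumed and only illustrates the mechanism.

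**Clock-time bias with zero drug effect.** Assumptions: 100 patients and 50 controls, 3 days, independent windows with SD 1, one value 1 h before and one 1 h after each intake, and intake times jittered with SD 0.5 h. The rhythm has amplitude A in window SDs. It is either a cosine peaking at 15 h or a linear drift A(t − 7)/15.

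The expected change across an intake at clock time d is:
- cosine: −2A·sin(π(d − 15)/12)·sin(π/12)
- linear: 2A/15 = 0.133A

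For the cosine with A = 1, the changes at 8, 12, 16 and 20 h are +0.50, +0.37, −0.13 and −0.50, with mean +0.06. Rises and falls largely cancel. A single intake at 8 h keeps the full +0.50.

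Share of 1,000 simulated studies in which a one-sample t-test on patient mean changes was positive at two-sided 5%:

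| Assumed intakes | Rhythm | A = 0.25 | A = 0.5 | A = 1.0 |
|---|---|---|---|---|
| 8, 12, 16, 20 h | cosine | 6% | 12% | 29% |
| 8, 12, 16, 20 h | linear | 13% | 36% | 92% |
| 8, 13, 18 h | cosine | 11% | 30% | 80% |
| 8, 13, 18 h | linear | 10% | 28% | 80% |
| 8 h only | cosine | 31% | 85% | 100% |
| 8 h only | linear | 6% | 12% | 37% |

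With A = 0 the rate was 4% to 6%. The patient-minus-control contrast at the same clock times gave 3.5% to 6.2% in every setting. That is expected, because the simulated controls share the patients' rhythm by construction.

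**On the ROC scale, which the article uses.** For one feature with SD 1, a pure clock shift δ gives AUC = Φ(δ/√2). The single 8 h intake with the cosine rhythm has mean shifts of 0.123, 0.251 and 0.495, so the AUC is 0.53, 0.57 and 0.64 with no drug effect. A true drug change of 0.5 within-subject SD also gives Φ(0.5/√2) = 0.64.

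**Cost of the reference.** Assume 4 intakes a day. This gives 100 × 3 × 4 = 1,200 patient windows and 50 × 3 × 4 = 600 sham windows, treated as independent.
- Before/after in patients: SE = √(2/1200) = 0.041 SD
- Patients minus controls: SE = √(2(1/1200 + 1/600)) = 0.071 SD, about 1.7 times as large

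**Why the level of clustering should be stated.** Two-group k-means was run on one feature, with 100 patients × 24 windows and a within-patient change of 1 SD. Accuracy with all values together was 0.67, 0.63, 0.59 and 0.56 at a between-subject SD of 0.5, 1, 2 and 3. With subject-centred values it was about 0.70 throughout (chance is 0.50). The loss is slight when subjects are alike and takes most of the signal when they differ widely.

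**The case against.** The strongest reply is that this is a condensed article on a dataset-building and method-development study. Both routes are optional, the hypotheses may be refined later, and analysis of the home data is deferred to later publications. A full protocol or analysis plan could supply the comparator, and nothing needed for it has been lost. This stands, and it lowers the severity. It does not remove the point, because the article states the contrast itself, and neither route offered can attribute a difference to medication.

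Several stronger readings are tempting, but the documents do not support them:
- **Clustering is pooled across subjects.** The article does not say so. Its On/Off example in Data Analysis compares a patient with himself or herself, which points to a within-patient intent.
- **The period after one dose runs into the period before the next.** Window lengths and dose intervals are not given.
- **Controls often share the patient's household.** Partners are one source of controls, but Subject Recruitment also lists hospital staff and the research consortium. No proportion is given.
- **Study day is lost when dates are removed.** The text gives an example of de-identification. It does not say that the order of days is discarded, and it keeps time of day.
- **False-positive rates are 23%, 69% or nearly 100%.** These follow from constant shifts of 0.05, 0.10 and 0.20 SD with SE 0.041. They require the same-sign shift at every intake, 1,200 independent windows, and a significance test that the article does not plan.

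**Conclusion.** The point holds as a gap in the stated analysis. A before/after-intake difference, or a classifier that separates the two, could not by itself be attributed to medication, because it could equally reflect time of day. The size of the bias is unknown. On assumed rhythms and intake times it runs from negligible to very large, and it depends mainly on whether rising and falling parts of the day cancel. The test rejection rates only gauge that range, since the article judges performance by confusion matrix and ROC curve.

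This is a cheap improvement and not an essential correction: the methods are optional and all the data needed are already collected.

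**What to change.** In Data Analysis, state that the before/after-intake result will be judged against a time-matched reference:
1. Give each control sham intakes at patients' intake clock times, run the same before/after analysis on the controls' home recordings, and report the patients' result relative to it.
2. As a check, repeat the analysis with patients' own non-intake windows, or with intake times shifted within the day.
3. Compute features relative to each subject's own level, by subject-centring or by clustering within patient. This agrees with the article's own same-patient example.

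**Cost.** Analysis code only, with no new data. The contrast has a larger standard error (about 0.071 against 0.041 SD on the assumptions above). It also assumes that controls share the patients' daily rhythm. Controls are not specifically age matched (Inclusion and Exclusion Criteria) and include hospital staff (Subject Recruitment), so this assumption should be stated. The within-patient check in step 2 does not depend on it.

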## Discussion

This paper describes the research protocol for a PD-monitoring study involving the use of smartphones and wearable sensors, also known as the KÄVELI project. This study aims to gather a dataset of 150 subjects to develop methods for monitoring PD-related motor symptoms in daily life. The user-friendly measurement setup is enabled by a data-collection system that consists of several microservices that automatically collect movement information when a subject wears the measurement device and registers their PD medication intake manually and through a smartphone app. There has been an increasing trend in studies toward home monitoring of PD with, for example, smartphones [7,23,37-39] and other wearable sensors [4,8,37,40-42]. In addition, several research groups have developed algorithms for recognizing various types of movements such as walking, running, and climbing stairs [31,32,43-45]. Based on the literature, there is a potential for monitoring PD with wearable solutions and machine-learning principles. These principles are applied in order to recognize the descriptive features of walking segments as well as to determine what sensors are required to achieve accurate recognition of the symptoms and evaluate their severity. The selection of correct features is important for linking the results to real physiological changes that are evident in the subjects’ walking.

Some mobile health platforms have been proposed to monitor PD patients during preset tests, such as PD Dr [6] and PD_manager [46], both of which have been tested on a relatively small set of patients with PD. HopkinsHD [47] is collecting data from free-living people and has been tested on a set of 226 subjects, both control subjects and patients with PD. These platforms have resulted in indications that home monitoring of PD patients is feasible. Our aim is to provide a platform that is suitable for long-term monitoring and uses the patients’ own smartphones or very affordable wearable sensors.

Most of the previous studies concentrating on the recognition of PD symptoms with wearable sensors have been conducted with relatively small datasets (10-50 subjects in total), which are feasible for proposing new methods in data collection or analysis, but not enough to validate the system with a larger variety of subjects. Some studies, however, have recruited more subjects [23,37,47]; these studies have collected larger datasets of several hundred subjects. Larger studies will be needed to validate systems before implementing them into a commercial product. The dataset collected in the KÄVELI project will be valuable in the investigation of PD motor symptoms in a quantitative manner, whereas the present clinical monitoring of PD is based on the subjective information provided by the patient and clinical observations by a neurologist or physiotherapist [25]. Despite the opportunities and new innovations presented by wearable sensors and machine learning, home monitoring has several practical challenges that must be evaluated and solved before they can become a common part of clinical routines. First, independent use of technological devices may create difficulties among the elderly, and acceptance of technology takes time and special effort in usability. Second, even if the technology itself is not new to the patients, severe motor symptoms and Off states combined with cognitive and memory disorders may complicate the registration of medication intakes or other tasks given to the patient [48]. Finally, even though home monitoring allows for measurements to take place in real-life situations that provide a more extensive view of symptoms, ensuring adherence to the measurement protocol is impossible outside of the clinical environment. For example, subjects can be reminded to register their medication intake, but they may forget to register it anyway, or the placement of the device might be changed unexpectedly.

The KÄVELI project’s measurement protocol aims to minimize these challenges by developing a user-friendly interface for the smartphone that registers medication intake and by providing written and spoken instructions for the use of all devices included in the study. The level of instruction also aligns with the subject’s confidence with technology. This is assessed by a question in the background interview: “How confident are you in using a smartphone?” which is also recorded in the study material. In addition, the physiotherapist can be reached by phone for further instruction if any challenges occur during the measurement period.

Despite the simple user interface of the smartphone (only one visible button for the medication recording), some subjects have had issues using the smartphone. Therefore, medications were also recorded in a paper format, which led to extra work for the subjects. This limitation, as well as any adverse effects or usability issues, will be recorded and considered in the development of the measurement system.

One potential limitation to the study is the recruitment of control subjects. It may be difficult to collect a dataset with a variety of mobility skills and still match the age group of patients with PD. We have recruited control subjects from among the patients’ family members, but this might also be considered a limitation. These challenges must be addressed accordingly when carrying out the study.

In conclusion, this study will provide quantitative information on PD motor symptoms and their statistical properties. The collected dataset will be used to develop algorithms and create tools for remote monitoring of PD progression by physicians and to assist with adjusting the medication.

